# Differentiated prevention and care to reduce the risk of HIV acquisition and transmission among female sex workers in Zimbabwe: study protocol for the ‘AMETHIST’ cluster randomised trial

**DOI:** 10.1186/s13063-022-06119-w

**Published:** 2022-03-12

**Keywords:** Effectiveness, Hidden population, Pragmatic trials, Randomised control trial, Respondent driven sampling, Sex workers

## Abstract

**Background:**

Female sex workers (FSW) in sub-Saharan Africa are disproportionately affected by HIV and are critical to engage in HIV prevention, testing and care services. We describe the design of our evaluation of the ‘AMETHIST’ intervention, nested within a nationally-scaled programme for FSW in Zimbabwe. We hypothesise that the implementation of this intervention will result in a reduction in the risk of HIV transmission within sex work.

**Methods:**

The AMETHIST intervention (Adapted Microplanning to Eliminate Transmission of HIV in Sex Transactions) is a risk-differentiated intervention for FSW, centred around the implementation of microplanning and self-help groups. It is designed to support uptake of, and adherence to, HIV prevention, testing and treatment behaviours among FSW. Twenty-two towns in Zimbabwe were randomised to receive either the Sisters programme (usual care) or the Sisters programme plus AMETHIST. The composite primary outcome is defined as the proportion of all FSW who are at risk of either HIV acquisition (HIV-negative and not fully protected by prevention interventions) or of HIV transmission (HIV-positive, not virally suppressed and not practicing consistent condom use). The outcome will be assessed after 2 years of intervention delivery in a respondent-driven sampling survey (total *n* = 4400; *n* = 200 FSW recruited at each site). Primary analysis will use the ‘RDS-II’ method to estimate cluster summaries and will adapt Hayes and Moulton’s ‘2-step’ method produce adjusted effect estimates. An in-depth process evaluation guided by our project trajectory will be undertaken.

**Discussion:**

Innovative pragmatic trials are needed to generate evidence on effectiveness of combination interventions in HIV prevention and treatment in different contexts. We describe the design and analysis of such a study.

**Trial registration:**

Pan African Clinical Trials Registry PACTR202007818077777. Registered on 2 July 2020.

**Supplementary Information:**

The online version contains supplementary material available at 10.1186/s13063-022-06119-w.

## Background

Effective tools for preventing and treating HIV are now widely availabl e[1]. Yet, globally, gaps in implementation remain especially among vulnerable populations [1, 2]. Eastern and Southern Africa is home to approximately half of all people living with HIV and just under half of all HIV-related deaths in 2019 [3]. Only 59% of those living with HIV in the region are virally suppressed [3–5]. Female sex workers (FSW) make up a small proportion of the population [6, 7] but bear a disproportionate burden of infection. The risk of HIV acquisition is up to 21 times higher for FSW than non-sex-working women aged 15–49 years [4, 8]. Further, sex work is directly or indirectly a cause of a high proportion (40–80%) of all new infections [4–9]. Implementing strategies that improve access, uptake and effective use over time of HIV prevention and treatment tools among FSW is needed urgently.

UNAIDS/WHO recommend targeted sexual and reproductive health services (including HIV related) for FSW, supported by peer-based community outreach. However, the optimal delivery model for such services in southern African contexts remains unclear. Effectiveness studies, especially randomised controlled trials (RCT), remain rare. In Zimbabwe, we previously conducted a cluster-RCT of an intervention comprising enhanced access to regular HIV testing, on-site initiation of ART, access to pre-exposure prophylaxis (PrEP), adherence interventions and intensified community mobilisation. The intervention improved rates of HIV diagnosis and treatment initiation. Viral suppression improved in both arms of the trial, but there was no significant difference in the proportion of all FSW with unsuppressed HIV infection between the arms [10].

Building on our previous work we have developed ‘AMETHIST’ (‘Adapted Microplanning: Eliminating Transmissible HIV In Sex Transactions’), a new intervention package with a greater focus on HIV prevention to complement the existing focus on HIV testing and treatment, and sexual and reproductive health more broadly. We hypothesise that this theory-based intervention, combining microplanning and self-help groups (SHG), can raise uptake and adherence to HIV prevention and treatment tools among FSW and thereby achieve our goal of reducing the proportion of FSW at risk of acquiring or transmitting HIV infection.

Here we formally describe the ‘AMETHIST’ intervention and its intended mechanisms of action and describe the design and analysis strategy for a pragmatic cluster randomised trial to determine the impact of the intervention on HIV transmission risk among sex workers.

### The AMETHIST interventions and its mechanism of action

A structured description of the AMETHIST intervention is shown in Table 1. It incorporates key elements of both the TIDIER framework [11] (elements 1–9, first column, Table 1) for intervention description and replication, and the Proctor framework for specifying implementation strategies [12]. Elements 10 and 11 of TIDIER relate to modifications and fidelity of intervention delivery in practice and so are more suitably reported at the end of the trial and therefore excluded here.

**Table 1 Tab1:**
[figure not shown]
Structured description of the AMETHIST intervention and Standard of Care within which this intervention is set, drawing on TIDIER and Proctor frameworks

### Standard of Care: the Sisters with a Voice programme

The Sisters with a Voice (‘Sisters’) programme was established in Zimbabwe in 2009 on behalf of the Ministry of Health and Child Care (MoHCC) and the National AIDS Council (Table 1) [13]. It operates nationally within 57 primary care clinics and provides services in line with WHO guidelines [14]. Sisters provides free condoms and contraception, provider-initiated HIV testing and counselling, HIV self-testing and counselling (and secondary distribution of self-test kits for partners), syndromic management of sexually transmitted infections (STIs), health education and legal advice supported by a network of peer educators. Additionally, clinics provide long-acting reversible contraception (implants), referral for cervical cancer screening and on-site access to PrEP. PrEP is available as part of national roll-out across all 22 sites participating in the trial. Stock of PrEP is coordinated and monitored nationally by MoHCC and at sites by the clinic manager. The programme is supported by over 400 sex worker peer educators trained to provide basic information and undertake condom distribution to peer FSWs; they earn $15USD *per month* as stipend. They mobilise FSW to attend clinical services and encourage uptake of HIV testing and support referral of FSW for antiretroviral therapy (ART) for those who test positive for HIV to government services for HIV care/ART initiation. Outreach worker (ORW) supervisors who are salaried social workers, meet with the peer educators at each site once a month as a group to discuss issues that have arisen. Programme data are collected electronically in real-time.

### AMETHIST intervention

In the AMETHIST intervention, we will introduce ‘microplanning’ and establish SHG, layered on top of the existing Sisters programme (Table 1). Through these components, the AMETHIST intervention seeks to strengthen FSW self-esteem, social support and group capacity [15, 16] as well as their motivation and opportunity to access services [17]. Through this focus on peer empowerment and community self-efficacy, the intervention seeks to enhance the capability of all FSW to overcome entrenched barriers to the adoption of behaviours that decrease HIV transmission (Fig. 1).

**Fig. 1 Fig1:**
[figure not shown]
Project trajectory outlining the intended mechanisms of action of the AMETHIST intervention

Both components of the AMETHIST intervention occur outside of formal clinical settings and are delivered in such a way as to be ‘HIV status neutral’. While the specific technologies and pathways of care for prevention and treatment differ, there are important similarities. Social and structural factors such as stigma, lack of social cohesion and the low socioeconomic status of female sex workers act as barriers to the uptake and effective use over time of both prevention and treatment tools. Condom use offers ‘dual protection’ from both HIV transmission and acquisition, and consistent condom use is strongly recommended for all FSW. Antiretroviral medications prescribed to be taken daily, albeit in different formulations and under different clinical supervision approaches, form a component of both treatment (as ART) and prevention (in the form of PrEP). The AMETHIST intervention seeks to reduce the risk of both HIV acquisition and transmission among FSW by targeting these common drivers, thereby reducing the role of commercial sex work in HIV transmission more broadly. Furthermore, a ‘HIV status neutral’ approach reduces a source of tension and mistrust between sex workers and retains a focus on the priorities and concerns they share as a community.

#### Microplanning

Peer-led microplanning aims to optimise programme coverage and support prevention and care uptake [18]. While it has been successful in India [19, 20] as a critical element of HIV prevention programming, it has not been widely implemented or evaluated in Africa. The sex workers who undertake the microplanning are called empowerment workers (EWs). EWs are FSW peer educators who additionally have a specified caseload of sex workers for whom they are responsible (*n* = 50–80), undergo additional training in data collection and interpretation and are expected to devote more time to microplanning than standard peer educators. Unlike the peer educators in the standard of care group, EWs are trained to identify geographic sex work ‘hotspots’, enumerate FSW working within those hotspots, assess their vulnerability and tailor support to each FSW’s level of social and clinical vulnerability. Hotspots are geographical locations where FSWs work and are places where high HIV risk behaviour may take place (or is negotiated) and includes streets, truck-stops, bars, lodges, hotels and brothels. Hotspots will be identified by EWs working in a geographic area. Care will be taken to ensure EWs have non-overlapping hotspots.

Microplanning incorporates a risk-differentiated approach to the support EWs provide to other FSW. EWs assess FSW’s vulnerability to HIV acquisition/transmission risk, and this guides the intensity with which microplanning is implemented. This vulnerability is assessed in the field using a simple algorithm based on age, duration in sex work, client numbers, condom use consistency, alcohol use and experience of violence (see Appendix Table A1). EW reassesses the risk of their case load at 3-monthly intervals (Table 1). FSW assessed as being at high risk will be followed up weekly, those at medium risk twice a month and those at low risk monthly. At each microplanning contact, EW provide support to individual FSW guided by their tracking data (e.g. revisiting previous discussions, reminding them about upcoming clinic appointments or ensuring they have an adequate condom supply) and remind women about clinic appointments. The microplanning process thereby generates data to inform subsequent contacts. EWs update the data, help analyse it, and meet with ORW supervisors weekly to plan whom to see each week and topics for discussion. Each EW earns a stipend of $50 USD per month. ORWs supervise empowerment workers across multiple hotspots in their respective sites. Each ORW has a caseload of 7-10 EW. Geographic hotspots will be remapped every 6 months and the size of the sex work population re-estimated so that the rate of programme coverage can be monitored.

#### Self-help groups

Self-help groups aim to build social cohesion and community empowerment. Each EW invites some of the FSW in her microplanning caseload to join a SHG comprised of 10–15 women who meet twice each month. FSW are invited to participate in SHG based on their level of vulnerability and their willingness/ability to attend meetings regularly. The EW facilitates the SHG, initially with the support of an ORW. FSW in the group receive training on how to participate, keep a register, manage money (including how to budget, save, open and manage a bank account) and keep minutes if required. Each SHG is assisted to identify priorities and take relevant action. Training is provided by the programme to support SHG with addressing their priorities. Over time, these groups strengthen programme ownership and community empowerment, to reduce HIV vulnerability and increase uptake of services among FSW [15, 21]. Although not all FSW will join the initial SHG, they provide a model of community leadership that goes beyond Sisters’ standard model of community mobilisation that relies on health-related workshops with a less interactive or sustained format.

### Process evaluation and costing

We will undertake a nested process evaluation which will draw on both quantitative programme data and qualitative assessments to monitor delivery and uptake of each programme component over time, examining ease of delivery, varying rates of participation by FSW and their experiences, perceptions and satisfaction levels. We do not describe this data collection in any further detail here but provide details in the trial protocol (see Appendix A2).

We will also determine the cost of the intervention components and the cost-effectiveness of the AMETHIST intervention, taking into account the potential reduction in transmissions via selling sex due to the reduction in the proportion of FSW who are at risk of either HIV transmission or acquisition. For this, we will use an existing individual-based dynamic stochastic model to predict the potential impact of this intervention on HIV incidence in the population of Zimbabwe. These methods are not discussed further here.

## Methods

### Trial design

The trial design is a cluster randomised controlled trial.

### Cluster definition and selection

A cluster is defined as the FSW population working in the geographic location (usually a town or business centre) where there is a government health clinic providing dedicated FSW services through the Sisters programme. Trial sites were purposively selected to be reflective of a range of settings, of adequate size to ensure participation of between 175 and 475 FSW annually (based on 2017 programme data) (mean 314; 50% seen for first time) and located at geographic spacing sufficient to ensure that the risk of contamination/spill-over of intervention effect between study clusters through FSW mobility and migration will be minimised (see Appendix Fig. A1).

### Randomisation

Twenty-two sites have been randomised (1:1) to receive the AMETHIST intervention in addition to standard of care or to continue with the standard of care alone. Randomisation was conducted in January 2019 at a public meeting with key stakeholders, MoHCC, district representatives and representatives of female sex worker community from the 22 sites. It was not possible to blind intervention staff or beneficiaries of services to the intervention allocation.

To minimise baseline imbalance between arms, restricted randomisation was used [22]. Restriction factors included province, number of FSW seen in the Sisters programme in 2017, mean age of first-time attenders, proportion of FSW attending the programme who were aged under 20 years of age, proportion of all attendees aware of HIV status, proportion of all HIV-positive attendees on ART and mean number of visits by attendees. Restricted randomisation resulted in a good balance of restriction factors between treatment arms (see Appendix Table A2). Restricted randomisation generated a list of 705,432 potential combinations from which 999 with the closest balance between arms were selected. Non-investigator attendees were invited to withdraw numbers from a bag to see which one of the 999 combinations was selected.

### Primary endpoint

The primary endpoint of the trial is a composite endpoint intended to capture the proportion of all FSW who are at risk of either HIV acquisition or HIV transmission as measured in a cross-sectional survey after 2 years of implementation delivery. Figure 2 shows how FSW primary endpoint status will be assessed (see also Appendix Table A4). At endline, all participating women will be identified with a binary endpoint measure: as either at risk of acquisition/transmission (red) or not at risk of acquisition/transmission (green). This means that both groups will include FSW who are both HIV positive (Fig. 2a) and HIV negative (Fig. 2b).

**Fig. 2 Fig2:**
[figure not shown]
Algorithm for the primary outcome: risk of HIV transmission among HIV positives. (**a**) OR risk of acquisition among HIV negatives (**b**). Y-chromosome test (Y-Chrom), GC (*Neisseria gonorrhoea* test), PrEP (pre-exposure prophylaxis), positive (+ve) and negative (−ve). FSW is at risk of transmission (red) or not at risk of transmission (green), yellow means additional tests are needed to classify them as ‘at risk’ or ‘not at risk’ of transmission/acquisition. Several questions were used to ascertain consistent condom (any condomless sex) (see Appendix Table A3). Asterisk indicates the following: in a sensitivity analysis, 350 fmol/DBS punch threshold will be used to classify FSW currently on PrEP as high vs low PrEP adherence

The determination of the primary endpoint incorporates data on four ‘domains’. First, their HIV status based on laboratory test at endline. Second, HIV-positive women are identified as either virally suppressed (< 1000 copies/mL) or not, based on viral load measurements at endline. Third, HIV-negative women are identified as either being on oral PrEP, or not. This is done first through self-report (where possible cross verified with programme data), and then, for those who report that they are currently taking PrEP, through requesting and analysing a blood sample for PrEP (tenofovir diphosphate) levels. Only those both reporting and having biological evidence of the presence of PrEP will be considered as ‘on PrEP’ (Fig. 2). Fourth and finally, among both HIV-positive and HIV-negative women, women will be classified as having had recent (in the past month) condomless sex unless she reports otherwise and there is not biological evidence to contradict this. This evidence will incorporate three types of information: first, women will be asked to self-report if they have had any condomless sex in the past month or not (see Appendix Table A3). For those who report no condomless sex, we will ask if they are willing to provide a sample for detection of Y chromosome, a biological marker of unprotected sexual activity with male partners [23]. In addition, all women will be offered testing for STIs including active syphilis, *Chlamydia trachomatis*, *Neisseria gonorrhoea* and *Trichomonas vaginalis*. We will consider women as having been validated as having had no recent condomless sex if she reports no condomless sex and has no evidence of vaginal *Neisseria gonorrhoea* or y chromosome in her vaginal sample (Fig. 2). Relevant data collection, questionnaire and laboratory methods are described in more detail below.

The trial protocol also pre-specifies a range of secondary outcomes summarised in Table 2.

**Table 2 Tab2:** Summary of secondary outcomes

1) Proportion of FSWs at risk of HIV transmission among HIV positives	
2) Proportion of FSWs at risk of HIV acquisition among HIV negatives	
3) Proportion of HIV-infected women who are infectious (viral load > 1000copies/μL)	
4) Proportion of FSWs reporting always using condoms with clients in last month who have laboratory evidence of STI	
5) Proportion of FSWs reporting always using condoms with clients in last month who have evidence of Y chromosome in vaginal specimen	
6) Proportion of FSW who have evidence of	
a. HIV testing in the last 6 months (among those now self-reporting HIV positivity)	
b. Having attended the Sisters clinic in the last 3 months	
c. Pre-exposure prophylaxis for HIV negatives	
d. Antiretroviral therapy for HIV positives	
7) Proportion of all FSWs who know HIV status (i.e. are diagnosed HIV positive or were tested HIV negative in last 6 months)	
8) Proportion of those taking ART who have (viral load > 1000 copies/μL) who have drug resistance	

### Inclusion and exclusion criteria for outcome assessment

Women are eligible for outcome assessment if they are aged 18 or older, currently working as a sex worker (has exchanged sex for money in the past 30 days) and living or working in the study site (for at least 1 month).

### Data collection: population sampling

The trial outcome will be assessed after 24 months of intervention using a respondent driven sampling (RDS) survey in each of the trial clusters. Initial ‘seed’ women who meet the study inclusion criteria will be selected after mapping sex work in that location [24]. Selection as a seed will be independent of whether they have accessed the Sisters programme. Each seed will start a recruitment ‘chain’ by recruiting up to two peers into the survey. Each subsequent respondent will be further provided with coupons to give to up to two peers to refer them into the study. Participants will receive financial compensation for completing the survey themselves, as well as for each of their recruits who participates. Recruitment will stop when approximately 200 women have been recruited in a given site (see sample size justification below). Ethical considerations including informed consent is described later and also in the Appendix (see Appendix A2).

### Data collection: questionnaires

Questionnaire data will be collected through self-administration directly onto tablet computers using an audio computer assisted survey instrument (ACASI) in part to minimise reporting bias. Trained research assistants will assist each FSW to log-in correctly and understand the use of the ACASI. The questionnaire will include questions on demographics, sex work, sexual behaviour and condom use, HIV testing history, ART use (including specific drug regimen), stigma, experience of violence, quality of life, mental health, substance use, general health, relationships with other sex workers and use of sexual and reproductive health services. We will collect data to determine personal network size for RDS adjustment: we will ask how many females sex workers the participant knows who are aged over 18, live at the site, who she has seen in the last month and who she would consider recruiting to the study. In addition, we will collect information from consenting women to allow us to link questionnaire data to Sisters programme data.

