### Analysis principles

Our primary analysis will compare FSW recruited in each community without considering direct contact with the intervention components (i.e. an ‘intention to treat’ approach). Data from individual FSW will be summarised for each cluster, and we will express the intervention effect using a prevalence ratio, prevalence difference and associated 95% confidence intervals.

We will calculate cluster summaries using the RDS-II methodology [31]. For unadjusted analysis, we will fit a linear regression model on the RDS-weighted cluster summaries, with a treatment dummy. We will use the *p*-value and confidence intervals for the coefficient of the treatment dummy.

Adjusted analysis will use the ‘two step’ method of Hayes and Moulton [32]. Age is specified a priori and will be included as a potential confounder that could affect the outcome. We will also adjust for other potential confounders that appear imbalanced by arm between survey participants recruited to the endline RDS surveys. Imbalance will be assessed using ‘eyeballing’ and expert opinion. Decisions about factors to be adjusted for will be made prior to the analysts having access to the complete primary outcome data. We will not adjust for any characteristics that may have been influenced by the intervention. To generate adjusted and RDS-II-weighted analysis, step 1, we fit a logistic regression model for each site with the primary outcome as the dependent variable, age and other variables as independent variables. This model will be used to ‘predict’ outcomes for each woman. The predicted values will be multiplied by the inverse of the degree (RDS-II) to account for the sampling design, normalised for the cluster, and cluster summaries calculated. Step 2, we will divide the cluster summaries used in the unadjusted analysis (accounting for RDS only) by the adjusted cluster summaries from step 1 to generate ‘residuals’. We will calculate the prevalence ratio using the regression model described above with the residuals as the dependent variable. We will calculate the ‘residual’ risk difference (RD) by subtracting the predicted prevalence from the RDS-II weighted observed prevalence in each cluster. We will fit a linear regression model on the residuals to calculate the adjusted RD and 95% confidence intervals.

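### The network-size question behind the RDS-II weights is narrower than survey eligibility on residence (and, read literally, on age), so weights can be wrong where the uncounted share of peers differs between women

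*Protocol article*

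**What the plan says.** All references are to the protocol article.

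- **Data collection: questionnaires.** The purpose of the question is explicit: "We will collect data to determine personal network size for RDS adjustment". It asks for the number of female sex workers "the participant knows who are aged over 18, live at the site, who she has seen in the last month" and, as a last condition, "who she would consider recruiting to the study".
- **Inclusion and exclusion criteria for outcome assessment.** On age: "Women are eligible for outcome assessment if they are aged 18 or older". On activity and place: "currently working as a sex worker (has exchanged sex for money in the past 30 days) and living or working in the study site", with a minimum of one month.
- **Cluster definition and selection.** The cluster is the sex-worker population that works in the location. Place of work, not residence, defines it.
- **Analysis principles.** "We will calculate cluster summaries using the RDS-II methodology". In the adjusted analysis, "The predicted values will be multiplied by the inverse of the degree (RDS-II) to account for the sampling design", and the result is then normalised for the cluster.
- **RDS diagnostics** and **Sensitivity analysis.** The plan compares reported degree and homophily by arm. It also repeats the primary effect without weights and with the Successive Sampling estimator.

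**The concern.** RDS-II treats a woman's chance of entering the sample as proportional to the number of eligible peers she is linked to, and weights her by the inverse of that number. The count should therefore cover the people who can pass coupons to one another, which is everyone eligible for the survey. Here the target population is defined by work, eligibility by living or working, and the degree by living alone. A woman whose peers mostly come in from elsewhere to work reports too small a degree and gets too large a weight. Read literally, the same holds for a woman whose peers are mostly 18.

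The degree enters both the unadjusted cluster summaries and the predicted values of the adjusted analysis, so any error reaches the primary result by both routes. The article gives reasons to take this seriously. It treats mobility between sites as a design issue, uses age in the vulnerability algorithm and as the pre-specified confounder, and accepts that the intervention might change network structure.

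**Working it through.** **1. The two definitions side by side**

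| | Eligible for the survey | Counted in the degree |
|---|---|---|
| Age | 18 and above | over 18 |
| Place | lives or works at the site, at least 1 month | lives at the site |
| Contact | none | seen in the last month |
| Recruitment | none | participant would consider recruiting her |

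The last two rows are usual ways of limiting a network question to active ties. The first two leave out people who are eligible. The gap on place is clear. The gap on age is one year and may be loose wording.

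**2. The plan's own figures**

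The plan gives no figure for this point. It gives a 30% outcome prevalence and a 30% relative reduction (30% to 21%, or 9 points), with 11 clusters per arm and about 200 women each. Its power at k = 0.25 can be checked, assuming a two-sided 5% test:

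- Variance = 0.30×0.70/200 + 0.21×0.79/200 + 0.25²×(0.30² + 0.21²) = 0.01026.
- √(10×0.09²/0.01026) = 2.81, which gives 80.2% power by the normal approximation and 76.2% by the non-central t with 20 degrees of freedom.

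The stated 78% lies between these. It does not depend on the degree wording.

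**3. When the weights go wrong**

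Let a woman have true degree d, of which a share u is not counted. Her weight is 1/[d(1−u)] in place of 1/d. If u is the same for every woman in the cluster, the factor 1/(1−u) cancels on normalisation and no weight changes. Only variation in u between women matters.

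**4. A simple illustration (assumed inputs)**

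Take two equal groups with risks of 40% and 20% (true prevalence 30%) and uncounted shares of 40% and 10%.

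- Over-weight of the first group = (1−0.1)/(1−0.4) = 1.5.
- Control arm: (1.5×40 + 20)/2.5 = 32.0%.
- Intervention arm, same structure, every risk multiplied by 0.7: (1.5×28 + 14)/2.5 = 22.4%.
- Ratio 22.4/32.0 = 0.70, unchanged. The difference is 9.6 points in place of 9.0.

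With uncounted shares of 50% and 0%, the over-weight is 2, the arms are 33.3% and 23.3%, the ratio is again 0.70 and the difference is 10 points.

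**5. A range with consistent ties (assumed inputs)**

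Let w be the share of women who work but do not live at the site, and h the share of their ties that go to one another. Mean degree is taken as equal in both groups. Residents then have a share x = w(1−h)/(1−w) of ties to non-residents. Relative weights are 1/(1−h) for non-residents and 1/(1−x) for residents. Outcome prevalence is 30% in residents.

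| w | h | Weighted share of non-residents | Shift, non-residents 40% | Shift, non-residents 50% |
|---|---|---|---|---|
| any | = w (random mixing) | w | 0 | 0 |
| 5% | 40% | 7.8% | +0.28 | +0.57 |
| 5% | 60% | 11.4% | +0.64 | +1.28 |
| 20% | 40% | 26.2% | +0.62 | +1.23 |
| 20% | 60% | 36.0% | +1.60 | +3.20 |
| 30% | 60% | 47.0% | +1.70 | +3.41 |

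Shifts are in percentage points. If both groups have 30% prevalence, the shift is 0 throughout. The positive sign follows from assuming higher risk in non-residents; lower risk would reverse it.

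**6. Effect on the ratio (w = 20%, h = 60%, non-residents 50%, true ratio 0.70)**

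- Same structure and same relative effect in both arms: 0.70.
- Clustering in the control arm only: control 37.2%, intervention 0.7×34.0 = 23.8%, ratio 0.64.
- Clustering in the intervention arm only: 0.7×37.2 = 26.0% against 34.0%, ratio 0.77.
- Same structure, but no effect in non-residents: the true ratio is (0.8×21 + 0.2×50)/34.0 = 0.79. The estimate is (0.64×21 + 0.36×50)/37.2 = 0.85.

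**The case against.** A reader might infer that the weights are wrong in both arms and that the primary estimate is therefore biased. The documents do not support this. They give no degree data, no share of non-resident or 18-year-old women, and no prevalence by residence. Within-cluster normalisation removes a uniform undercount. Nor should a shift of 2 or 3 points in one arm's prevalence be set against the planned 9-point effect as if the two were comparable, because the trial estimates a contrast. With the same error in both arms and a uniform relative effect, the ratio does not move. This part of the objection stands in full.

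The article may also paraphrase the question. The questionnaire is not shown, and the fielded wording may already say live or work. This stands too, and the fix has to allow for it.

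Third, safeguards are already planned: comparisons of degree and homophily by arm, and an unweighted analysis. They bear on error that differs by arm, the main route to a biased ratio. This stands only in part. The comparisons use the same incomplete count, the Successive Sampling estimator also depends on degree, and the unweighted analysis shows sensitivity without correcting anything. None of them recovers peers who were never counted, and a later analysis plan could not do so either.

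**Conclusion.** The inconsistency is real and concerns a stated rule, not an omitted detail: the degree question is narrower than eligibility on residence and, literally, on age. Its consequence is conditional. Individual weights are wrong where the uncounted share of peers differs between women. Cluster prevalence is biased if that share also relates to the outcome. The ratio is biased if the error differs by arm, a risk the article recognises for network structure, or if the intervention effect differs by residence.

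With 5% to 30% non-residents, 40% or 60% of their ties to one another, and their outcome prevalence at 30% to 50% against 30% in residents, the shift in prevalence is 0 to about 3 points (largest value 3.4). In the single scenario worked above, a true ratio of 0.70 is estimated as 0.64 or 0.77 when clustering occurs in one arm only. All these inputs are assumptions, so the figures show what is possible and not what happened. The point is minor to moderate and worth correcting because correction is cheap.

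**What to change.** Align the question with eligibility: female sex workers she knows, aged 18 and above, who live or work at the site, whom she has seen in the past month and would consider recruiting. The recruiting condition stays, since it bears on who could receive a coupon.

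The Trial status section plans to complete data collection by 31 December 2021, before the article appeared in March 2022, so rewording was probably no longer possible. The first step is to check the fielded question.

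- If it already matched eligibility, correct the sentence in the article.
- If it was fielded as printed, state the limitation, report the planned unweighted estimate next to the primary one, and examine results by respondents' residence if that was recorded. Imputing the missing peers is not advised, since the article names no data source for it.

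The cost is one sentence of text, or a short limitation paragraph and one added table. No new data collection or change to the primary estimator is needed.
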